#### Intra-Assay Variations

To evaluate the reproducibility of each salivary and hair biomarker, the within-subject standard deviation (Sw) will be calculated by obtaining the square root of the sum of the within-subject variance and the error variance estimated in a linear random-effects model. The mean intra-assay coefficients (ICCs) will be determined for each biomarker and interpreted as follows: 0 (SD 0.2), poor agreement; 0.3 (SD 0.4), fair agreement; 0.5 (SD 0.6), moderate agreement; 0.7 (SD 0.8), strong agreement; and >0.8, almost perfect agreement.

#### Secondary Outcome Measures

Secondary outcome measures include any clinical macular changes or retinal function measured with the ETDRS scale, CSV-1000 chart, and ancillary tests, such as the VFI, OCT, and OCTA. In addition, several patient-reported variables, such as self-recorded sleep diaries, perceived stress, and functional status will be recorded.

#### Covariates and Confounders

Several variables will be measured as potential covariates, including preintervention sleep quality scores, concomitant procedures, medical comorbidities, alcohol use, antianxiety medications or other nonprescribed medications used to help with insomnia and anxiety relief, tobacco use, and nonsteroidal anti-inflammatory drug (NSAID) and others anti-inflammatory drug treatment. In addition, basic demographic information will be obtained.

### Ethical Considerations

The protocol was reviewed by the local Institutional Review Board of the East Health Area of Valladolid (CASVE 21-520) and will be registered with ClinicalTrials when a start date is decided.

Informed consent will be obtained from each patient in the preintervention period, which must be signed, thumb-imprinted, or recorded by the patient and collected by a coached research assistant, when necessary.

Privacy and confidentiality will be guaranteed for each patient, and the study will be conducted in accordance with the principles of the Declaration of Helsinki.

### Data Management, Analysis, and Additional Information

#### Data Management

In the clinical trial, data handling will be managed by a third-party agency. The investigators, patients, and clinical staff rating or applying therapies will not have access to information until the data analysis is completed by predetermined statisticians. They will also not be aware of the allocation of patients in the trial. Data entry into the virtual system will also be managed by the third-party agency.

Patients’ information will be encrypted in a virtual database, secured, and password-protected. Only the data monitoring committee (DCM) will have access during the trial. Data coding will begin at randomization; SAS will generate an alphanumeric code for each block. An ID number will be assigned to each patient. If a major adverse effect occurs, it will be identified by the ID number.

The software will record any changes made by any person involved in the functioning of the program. The user ID will identify people who make any changes to the system, and this information will be used for the purpose of auditing the trial. During a regulatory audit, the auditors can verify any changes that occur in the system and data. All data will be regularly backed up to a password-secured database.

#### Data Monitoring

The DCM will comprise a data manager, a database programmer/designer, a medical coder, a clinical data coordinator, a quality control associate, and a data entry associate. A member of the DCM can have 1 or more duties. The DCM will be established according to the Spanish Agency of Medicines and Medical Devices (AEMPS) rules. According to Royal Decree 1090/2015, of December 4, the AEMPS is the regulatory authority responsible for clinical trial oversight, approval, and inspections in Spain and is attached to the Ministry of Health. The Institutional Ethics Committee will review and approve the clinical trial applications prior to the AEMPS initiating its review and approval process.

Data monitoring will take place in a pre-established room, with easy access to data, inside the institution but not in the same room where the trial is performed.

#### Interim Analysis

The clinical trial will have 4 major evaluation time points of interventions, that is, every week after V_0_ and 4 weeks and 6 months postintervention. In each visit for application of the intervention, the patient’s personal diary will be reviewed by the clinical staff. They have the responsibility to notify the DMC about eventual minor or major adverse effects.

Adverse events will be recorded from the start of stimulation through the end of the study. All adverse events regardless of attribution to OM and any unexpected adverse event due to the optical filters will be recorded using standard adverse event forms. Adverse events will be measured in several areas: seriousness, severity, length of duration, and any causal relationship, if any, with the intervention. Serious adverse events will be defined as those that are life threatening/disabling, require hospitalization, or result in death.

Patients who develop any adverse effect will be followed up. The DCM will have unblinded access to all patient data and will discuss the adverse events at a meeting. The decision of allowing a patient to withdraw from the study will be made by a majority consent of 50% or more.

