#### Oral Melatonin (6 mg)

Patients will be asked to intake a 6 mg melatonin dose orally once a day for 30 days in the evening (22:00 P.M. with a margin of 30 minutes before and after) to activate its sleep-promoting effects approximately 2 hours after intake, avoiding fatigue and sleepiness during the daytime [96-99].

Although the chosen dose is safe to obtain the desired effect, patients will be prompted to report any possible side effects, if present, during the intervention period [79,81,82,100]. If they experience unbearable side effects, they will have to discontinue the OM intervention. If they wish, they can participate in the SWL-blocking intervention and will be evaluated over the 4-week follow-up period.

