#### No Intervention

The purpose of this arm is to serve as the procedural control, so patients in this group will be asked to fill their sleep diaries at home only for the first 2-week period after trial commencement. They will be chosen as comparator to avoid performance bias and other biases related to loss of binding in the trial.

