### Data Collection and Outcome Measures

#### Baseline Assessments and Frequency of Follow-Up Assessments

A full list of assessments obtained at each time point is summarized in Table 3.

We will obtain baseline assessments during each patient’s screening visit. These measures will include, but will be not limited to, demographics, comorbidities, subjective sleep quality and perceived stress rating, ophthalmic and laboratory outcomes, and patient-reported outcomes specific to the planned intervention.

Initial follow-up assessments will be obtained at 1, 2, 3, and 4 weeks after the start of the intervention. Patients will also be asked to return for postintervention follow-up visits 6 months after the intervention. These visits will be scheduled at the beginning of the study. Patients unable to attend any in-person visit will be asked to at least provide all subjective patient-reported outcomes over the phone or via an electronic survey for that visit in order to facilitate retention and optimal follow-up.

Sleep quality level, laboratory outcomes, ophthalmic clinical outcomes, questionnaire patient-reported outcomes, and potential complications will be gathered during these visits.

**Table 3 table3:** Assessments and follow-up.

Clinical and laboratory event	V_–1_^a^ (–4 weeks)	V_0_ (0 weeks)	V_1_ (1 weeks)	V_2_ (2 weeks)	V_3_ (3 weeks)	V_4_ (4 weeks)	V_F_ (6 months)
Screening	✓^b^	—^c^	—	—	—	—	—
Clinical	—	✓	—	—	—	✓	✓
Physical examination	—	✓	—	—	—	✓	✓
Salivary sample collection	—	✓	✓	✓	✓	✓	—
Hair sample collection	—	✓	—	—	—	✓	—
STAI^d^ questionnaire	—	✓	—	—	—	✓	—
ESS^e^ and PSQI^f^ questionnaires	—	✓	—	—	—	✓	—
Inclusion criteria	✓	—	—	—	—	—	—

^a^V: visit; V_–1_, screening visit, when inclusion and exclusion criteria will be checked; V_0_, visit to assess baseline characteristics; V_1_-V_4_, visits during the intervention period (every week); and V_F_, final visit after 6-month follow-up.

^b^✓: applicable.

^c^Not applicable.

^d^STAI: State-Trait Anxiety Inventory.

^e^ESS: Epworth Sleepiness Scale.

^f^PSQI: Pittsburgh Sleep Quality Index.

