### Statistical Analysis

#### Sample Size Calculation

A sample size estimation of 48 patients (n=12, 25%, per group) was calculated for a target power of 80% and considering an α (probability of rejecting a true null hypothesis) of 5% and an actual power of 80.02%. Cohen d was 1.2 [101]. Due to the possible overestimation of the effect size in pilot studies, an effect size of 0.6 (medium-high) was chosen for this study. We calculated a total sample size of 60 participants (a total of 15, 25%, patients per group), adding approximately 20% (3 more patients per group than before) to manage possible dropouts [102-105].

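### The adverse event recording rule sets a lower bar for melatonin than for the filters, so recorded event rates could differ by arm because of the rule alone

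*Protocol article*

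**What the plan says.** The recording rule stands in the Interim Analysis section of the protocol article: "All adverse events regardless of attribution to OM and any unexpected adverse event due to the optical filters will be recorded". The window is set just before it: "Adverse events will be recorded from the start of stimulation through the end of the study". The same section gives the occasion for detection. Clinical staff review the patient's diary "In each visit for application of the intervention" and must notify the monitoring committee of minor or major adverse effects. It adds: "Patients who develop any adverse effect will be followed up".

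Other sections bear on the point:

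- Oral Melatonin (6 mg): "patients will be prompted to report any possible side effects, if present, during the intervention period". The section on optical filters has no matching sentence.
- No Intervention: control patients "will be asked to fill their sleep diaries at home only for the first 2-week period after trial commencement". Table 1 gives them no diary in the 30-day intervention period.
- Baseline Assessments and Frequency of Follow-Up Assessments: "potential complications will be gathered during these visits". Here no arm is singled out, and Table 3 schedules V1 to V4 and VF without distinguishing arms.

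**The concern.** A comparison of event rates between arms is fair only if each arm records events under the same threshold, over the same window and with the same prompting. The stated rule differs on the first, is unclear on the second, and is explicit about prompting only for melatonin.

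Two things are at stake. First, the complaints that matter most for melatonin are also common background in this population. The Discussion lists headache and insomnia among its minor adverse effects, while the section on the significance of the study links RP itself to headaches and sleep disturbance. Only equal capture in the no-intervention arm can separate the two. Second, filter tolerability is a foreseeable issue. Table 2 requires enough visual function to tolerate the filters and see through them, and the Limitations section names this as a recruitment difficulty. A complaint that is foreseen is one that a filter rule limited to unexpected events may leave off the form.

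**Working it through.** **Text check.** The plan states no event rate or count here, so there is no figure of its own to reproduce. Side by side:

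| Element | Melatonin | Filters | Control |
|---|---|---|---|
| Threshold for the form | any event, whatever its attribution | unexpected and due to the filters | none stated separately |
| Start of recording | stimulation (not given) | stimulation (not given) | stimulation (not given), and no intervention starts |
| Stated detection route | diary review at intervention visits | diary review at intervention visits | no intervention applied; no diary in the 30 days (Table 1) |
| Explicit prompt for side effects | yes | none stated | none stated |

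The first clause of the rule could be meant for every patient in the trial. The second clause would then add nothing, since an unexpected filter event is already an adverse event. Giving each clause a function leads to two thresholds. The sentence is therefore unequal on its natural reading and ambiguous at best. Both clauses apply to the combined arm. They also leave open which one governs a patient who stops melatonin and continues with the filters, as the Modification/Discontinuation section allows.

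**Illustration of size.** Inputs:

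- n = 15 per group (Sample Size Calculation).
- p = true risk of an event, the same in every arm. Assumed 20%, 40% or 60%.
- c = share of those events that reaches the form in the arm under the narrower rule. Assumed 0%, 25%, 50% or 100%.
- Capture in the melatonin arm is taken as 100%.

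Formulas: expected recorded events are n × p under the wide rule and n × p × c under the narrow rule. The artificial risk difference is p − p × c = p(1 − c).

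| p | Melatonin arm, n × p | Narrow rule, c = 0% | c = 25% | c = 50% | c = 100% |
|---|---|---|---|---|---|
| 20% | 3.0 | 0 (20 points) | 0.75 (15 points) | 1.5 (10 points) | 3.0 (0 points) |
| 40% | 6.0 | 0 (40 points) | 1.5 (30 points) | 3.0 (20 points) | 6.0 (0 points) |
| 60% | 9.0 | 0 (60 points) | 2.25 (45 points) | 4.5 (30 points) | 9.0 (0 points) |

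Example: for p = 20% and c = 50%, 0.20 × (1 − 0.50) = 0.10, or 10 points, with no true difference between arms. Under one common rule c is 100% everywhere and the artefact is zero.

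**The case against.** The strongest reply is that the first clause, taken alone, covers every event in every patient, so that a control patient's headache would be recorded. The sentence is not expressly limited to the melatonin arms. This reading is possible, though it makes the filter clause redundant.

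Second, some text is neutral between arms. Complications are gathered at visits that Table 3 does not restrict by arm, staff must notify minor or major adverse effects, and patients with any adverse effect are followed up. These routes may bring some filter and control events to light. They set no common threshold, start point or question for the adverse event form.

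Third, the reference to stimulation can be taken as a slip for the start of the intervention period. It then needs only an editorial correction and does not by itself show that controls are excluded. That is fair. Likewise, the absence of a prompt in the filter section carries little weight in a condensed article, where elicitation wording and event definitions may sit in the full protocol. The unequal threshold is different, because the article states it.

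Fourth, visual function is measured in any case: acuity, contrast sensitivity, visual field and OCT are secondary outcomes. Objective deterioration would therefore be seen outside the form, although a complaint felt only while wearing the lens might not be. The article also does not list which filter events count as expected, so the exact losses cannot be named.

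**Conclusion.** The point holds as a defect in a stated rule. On its natural reading, expected filter complaints need not be entered on the adverse event form, and capture in the filter-only and control arms may be lower than in the melatonin arms. Recorded rates could then differ by arm through the rule alone. At an assumed true risk of 20%, the artefact is 10 points with 50% capture and 20 points with none. Both the risk and the capture share are assumptions, and zero capture is the extreme case.

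A reader might go further and infer that tolerability cannot be compared at all, that filter harms never reach the monitoring committee, or that control events are certain to be missed. The documents do not support this, given the ambiguity of the first clause and the arm-neutral text. Nor does the rule distort who stops melatonin: discontinuation depends on the individual patient's side effects and not on rates compared between arms.

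**What to change.** In the Interim Analysis section, replace the two sentences on window and threshold with one rule for all four arms:

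- Record every adverse event, expected or not and whatever its attribution.
- Record from V0 (or randomization) to VF, and delete the reference to stimulation.
- Elicit events with the same question in every arm at the scheduled visits, V1 to V4 and VF.
- Enter relation to melatonin and relation to the filters as two separate fields on the form, judged after the event has been recorded.

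The detection sentence should refer to these visits and not to visits at which an intervention is applied. The Results section says that the trial has not started, so the cost is protocol and form wording plus a few more minor-event entries at visits already planned.

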### Statistical Analysis

#### Sample Size Calculation

A sample size estimation of 48 patients (n=12, 25%, per group) was calculated for a target power of 80% and considering an α (probability of rejecting a true null hypothesis) of 5% and an actual power of 80.02%. Cohen d was 1.2 [101]. Due to the possible overestimation of the effect size in pilot studies, an effect size of 0.6 (medium-high) was chosen for this study. We calculated a total sample size of 60 participants (a total of 15, 25%, patients per group), adding approximately 20% (3 more patients per group than before) to manage possible dropouts [102-105].

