Melatonin is an endogenous hormone that has been implicated in a variety of biological processes, including antioxidant, anti-inflammatory, and neuroprotective activities [56,57]. Melatonin is released from the pineal gland in a circadian fashion, which is controlled by the SCN. However, many other tissues and organs also synthesize melatonin. In the retina, it is mainly synthesized by photoreceptors and is involved in the modulation of neuronal activities. Its circadian production results in a high concentration at night and a low level during the day, although its amount is small compared to its pineal counterpart [7,51,58].

Oxidative damage has been proposed to be an important contributor to cone death in RP, and antioxidants may prevent cone damage in RP by reacting with free radicals produced during light absorption [59]. Melatonin behaves like synthetic mitochondria-targeted antioxidants, which are concentrated in the mitochondria at relatively high levels [51,58]. It exerts its antioxidant actions in the eye via several mechanisms, including direct ROS scavenging, stimulating antioxidant enzymes, improving the functioning of the mitochondrial electron transport chain (ETC), reducing the extent of electron leakage from the mitochondrial complexes, and improving the efficacy of other antioxidants. As mentioned before, mitochondria from photoreceptors, retinal ganglion cells, and RPE cells are the main targets of ROS produced by the ETC, and thus, melatonin may prevent mitochondrial damage in patients with RP [7,51,58,60,61].

However, it has also been demonstrated that daily administration of appropriately timed melatonin can synchronize the circadian clock [62-66] in patients with sleep disorders; its use is even recommended by the Standards of Practice Committee of the American Academy of Sleep Medicine [67]. The phase-shifting effects of melatonin are essentially opposite to those of light. It can phase-shift the endogenous circadian clock and, in the absence of light, entrain the sleep-wake and neuroendocrine rhythms (cortisol) [61]. Therefore, it is likely that OM may also be effective in sleep and circadian rhythm management in patients with RP. However, to the best of our knowledge, no previous RCT has investigated the potential additive benefits of adjunctive SWL-blocking glasses plus OM in improving sleep, perceived stress, and the circadian rhythm in patients with RP.

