The aim of this study is to assess the efficacy of OM combined with SWL-blocking filters in patients with RP who have sleep disorders and stress compared to any intervention alone or no intervention. We hypothesized that both interventions would improve their sleep quality, reduce their perceived stress levels, and shift their circadian rhythm to morningness.

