### Choice of Comparators

To date, therapeutic approaches for RP are restricted to slowing down the degenerative process; treating ocular complications, such as cataracts and macular edema; and helping patients cope with the social and psychological impacts of blindness. In addition, the evidence from RCTs on the visual protective effects of vitamins and nutritional supplementations in patients with RP is limited and in some cases contradictory. Moreover, as mentioned before, few studies on the effects of blocking SWL on visual discrimination capacity in patients with RP have been reported. In addition, in clinical practice, there is insufficient experience to recommend the use of optical absorbing filters, since their potential effects on regulating the human internal circadian (24-hour) clock in patients with RP are yet unknown.

For this reason, the intervention groups will consist of SWL blocking alone (SWL group), OM therapy alone (OM group), and SWL blocking plus OM therapy (SWL+OM group) in order to determine whether there is any summative effect. No intervention has been chosen for comparison to avoid performance bias and other biases related to loss of blinding in the trial. Therefore, as several treatments have been proposed to slow down the degenerative process and the current evidence from their results is still limited, no intervention as the control group is justified for this study.

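### The single stated power of 80% cannot cover both the combination versus each single treatment and the combination versus no intervention, and the sample size text does not say which comparison it refers to

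*Protocol article*

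**What the plan says.** All references are to the protocol article.

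- **Aim (Background and Rationale).** The combination of oral melatonin (OM) and short-wavelength light (SWL) filters is to be assessed "compared to any intervention alone or no intervention".
- **Hypothesis (same section).** "We hypothesized that both interventions would improve their sleep quality, reduce their perceived stress levels". I read this as each treatment being expected to work.
- **Reason for the arms (Choice of Comparators).** The two single-treatment arms and the combination arm are there "in order to determine whether there is any summative effect".
- **Prior evidence (Background and Rationale).** To the authors' knowledge, "no previous RCT has investigated the potential additive benefits of adjunctive SWL-blocking glasses plus OM" in patients with retinitis pigmentosa.
- **Sample Size Calculation.** "A sample size estimation of 48 patients (n=12, 25%, per group) was calculated for a target power of 80"%, "considering an α (probability of rejecting a true null hypothesis) of 5"% and "an actual power of 80.02"%. The effect size is given as "Cohen d was 1.2". The paragraph then warns that pilot studies may overstate effects, says that 0.6 was chosen, and arrives at 60 patients (15 per group) by adding about 20% for dropout to the same 12 per group. It names neither an endpoint nor a pair of arms.
- **Named comparisons elsewhere.** The Statistics section compares intervention arms with the control in the hormone model. The closing Conclusion speaks of the combination being superior to no intervention.

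**The concern.** The protocol publishes one power figure for a four-arm trial whose question has two parts: whether the combination beats no treatment, and whether it beats either treatment alone. The second part is the reason for having separate single-treatment arms. It is also the harder one, because the comparator is itself expected to work. A reader who sees 80% in the sample size section has no reason to think that it applies to only one of these questions.

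What is at stake is how a null result would be read. A non-significant difference between SWL+OM and SWL, or between SWL+OM and OM, set beside a claimed power of 80%, could be taken as evidence that adding the second treatment brings nothing. With 12 to 15 patients per arm, the data could seldom support that conclusion.

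**Working it through.** **Inputs from Sample Size Calculation:** 12 per arm before dropout, 15 enrolled; alpha 5% (sidedness not stated, two-sided assumed); d=1.2; chosen effect size 0.6; stated power 80.02%. Missing Data expects 5% to 10% dropout, so 15 enrolled leaves 15 × 0.90 = 13.5 to 15 × 0.95 = 14.25 evaluable per arm. The columns for 12 and 15 below bracket that.

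**Formula.** Two-sample t test with n per arm: df = 2(n − 1), noncentrality = d × √(n/2), power from the noncentral t distribution.

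**Step 1: reproduce the plan's figure.** With n=12 and d=1.2, noncentrality = 1.2 × √6 = 2.94, df = 22 and power = 80.2%, against 80.02% stated. Twelve is the smallest n that reaches 80%, and 4 × 12 = 48. Dropout: 12/0.80 = 15 per arm, 60 in total. Alternatives fit less well:
- A one-sided test needs 10 per arm and gives 88.5% at 12.
- A four-group ANOVA with f=0.6 needs 36 in total and gives 93.1% at 48.
- A four-group ANOVA with f=0.5 also gives 48 (80.3%), but 0.5 is not a stated input.

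So, from the stated inputs, 48 and 60 follow from d=1.2 in one pairwise comparison, not from 0.6.

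**Step 2: relate the contrasts.** On a common SD,

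d(combination vs control) = d(single vs control) + d(combination vs single).

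If the single treatment has a positive effect, the last term is strictly smaller than the left-hand side. One d fits both contrasts only if the single treatment does nothing.

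**Step 3: power by size of the pairwise difference (two-sided 5%).**

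| Difference (SD) | 12 per arm | 15 per arm |
|---|---|---|
| 1.2 | 80% | 89% |
| 0.9 | 56% | 66% |
| 0.6 | 29% | 35% |
| 0.3 | 11% | 12% |

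The smallest difference detectable with 80% power is 1.20 SD at 12 per arm and 1.06 SD at 15.

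**Step 4: place combination versus single in the table.** The documents give no add-on effect, so these are scenarios:
- 1.2 is combination vs control and a single arm gives 25%, 50% or 75% of it (assumed): the add-on is 0.9, 0.6 or 0.3 SD.
- 0.6 is combination vs control and a single arm gives half (assumed): the add-on is 0.3 SD, with 11% to 12% power.
- Each single has 0.6 and the effects add fully: combination vs control is 1.2 and the add-on is 0.6 SD, with 29% to 35% power.
- Each single has 1.2 and the effects add fully: combination vs control is 2.4 and the add-on is 1.2 SD. In this case 80% is kept.

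**Step 5: precision.** The 95% CI half-width for a two-arm difference is t(0.975, df) × √(2/n). At n=12: 2.074 × 0.408 = 0.85 SD. At n=15: 2.048 × 0.365 = 0.75 SD. An observed difference of zero would therefore still be compatible with an add-on effect of 0.6 SD.

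**The case against.** The sample size text ties 1.2 to no pair of arms and no endpoint. A reader might infer that d=1.2 cannot possibly apply to combination versus single treatment. The documents do not support that: the last scenario in Step 4 keeps 80%. It needs 2.4 SD against control, which is hard to credit when the protocol itself regards 1.2 as a possible overestimate, but it is not excluded. Nor does the absence of an earlier randomised trial of the combination in this disease prove where 1.2 came from, since its source is not shown.

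A reader might also infer that the authors intend to read a null result as no added benefit. No passage says so. The comparisons the plan does name are against control, the abstract calls the trial a feasibility study, and the order of comparators in the aim is not a stated ranking. The misreading is a risk that I infer.

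The shares of 25%, 50% and 75% are mine. No interaction test is named, and fully additive effects would give a zero interaction, so the point rests on the pairwise contrasts alone.

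Finally, it can be said that power for further contrasts belongs in a fuller document. That is fair as to extra detail. It does not dispose of the point, because the article publishes a power figure without limiting it and makes combination versus single part of its aim.

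**Conclusion.** The point stands in this form: one d and one 80% cannot describe both combination versus single and combination versus no intervention if the single treatments work as hypothesised, and the text does not say which comparison is meant. That follows from the identity in Step 2 and needs no assumed effect size. It also holds if 1.2 is accepted in full.

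The size of the shortfall depends on the effect. At the protocol's own 0.6, every pairwise contrast, including active versus no intervention, has about 29% to 35% power. An add-on of 0.3 SD, which assumes that a single arm delivers half of a 0.6 effect, has 11% to 12%. These figures assume a two-sided 5% t test, equal SDs and no multiplicity adjustment. A non-significant combination-versus-single result could not by itself show that there is no summative effect.

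**What to change.** In Sample Size Calculation:

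1. State which endpoint, which pair of arms and which effect size the power refers to.
2. Reconcile 1.2 with 0.6 and restate the power for the value retained. Simply relabelling the 80% as active versus no intervention would not do, because 0.6 gives 29% to 35% there as well.
3. State that 80% does not cover SWL+OM versus SWL or SWL+OM versus OM, and give the expected 95% CI half-width for these contrasts: about 0.85 SD at 12 and 0.75 SD at 15 per arm.
4. State that these contrasts will be reported as estimates with confidence intervals, and that a non-significant result will not be read as absence of a summative effect.

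The cost is a few sentences and a less favourable stated power. No extra patients or procedures are required if the sponsor keeps 60 and describes what it can show. If 80% power at 0.6 is wanted instead, a pairwise comparison needs 45 per arm (4 × 45 = 180), or 45/0.80 = 56.25, rounded up to 57 per arm (228 in total), with the same dropout allowance. The trial has not started, so the text can still be changed before any data exist.
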